### **Lumbar puncture**

The screening lumbar punctures will be performed i) to provide safety information e.g. exclusion of infection and ii) to assess the levels of CSF amyloid beta, CSF total tau and CSF phospho-tau 181. The CSF collection will be performed according to the standard operating procedures of the study centre, by a physician expert in this procedure, and considering the recommendations outlined in the articles cited in the next paragraph in an effort to limit the frequency and severity of post-lumbar puncture headache (PLPHA). Subjects will remain supine for 1 hour following the procedure.

The most common adverse event following lumbar puncture is post-lumbar puncture headache (PLPHA), which is thought to be related to persistent CSF leakage, causing a fall in CSF pressure. Published data indicates the incidence of headache in subjects following diagnostic lumbar puncture ranges from 3.3 to 59.2%. A recent review of CSF sampling in both healthy subjects and patients with AD (n=78) reported that serial sampling (6-10 collections of 6mL CSF over a day) was associated with an overall incidence of headache of 35%, the majority of which were mild, with 23% rated as moderate. There was a 24% incidence of back pain which was considered related to the prolonged bed rest (24 hour) required following serial sampling [[Jhee, 2003](#)]. The size and shape of the needle, but not the duration of the recumbence, have been shown to affect the incidence of PLPHA. These considerations are included in a report from the Therapeutics and Technology Subcommittee of the American Academy of Neurology (AAN) [[Evans, 2000](#)]. The importance of a smaller needle size in preventing PLPHA has been reaffirmed in a more recent report from the same Subcommittee [[Armon, 2005](#)]. If necessary this may be treated with an epidural blood patch which generally relieves the headache but is not normally deemed necessary. The technique for this procedure is described in [Appendix 6](#).

### **Insertion of CSF catheter and continuous CSF drainage**

Continuous CSF sampling will be performed i) to better understand the pharmacodynamics of GSK933776, ii) to assess for quantifiable levels of GSK933776 and iii) to provide safety information on potential adverse events. CSF samples will be continually obtained from all enrolled subjects for **22** hours and 3 mL CSF sample will be collected at each hour (as described in the Time-Events Table, Section [4.6](#)). The continuous CSF collection will be performed according to the standard operating procedures of the study centre, by a physician expert in this procedure, and considering the recommendations outlined in the articles cited in the next paragraph in an effort to

limit the frequency and severity of PLPHA. Subjects will remain supine for 1 hour following the procedure.

There is limited literature on the risk of adverse events specific for use of CSF catheters for continuous drainage, Walchenbach *et al* [Walchenbach, 2002] reported bacterial meningitis in 2 of 38 patients – both recovered after antibiotic therapy - and drain replacement in 5 of 38 patients. Other adverse events that have been described and assumed reason:

- Root irritation (radicular pain, back or leg pain/paresthesia) – catheter proximity to nerve root
- Pneumocephalus – introduction of air into subarachnoid space
- Infection (meningitis) – bacterial contamination of drainage line
- Subdural haematoma and secondary intracranial haematoma – attributable to CSF over-drainage or sudden reduction in CSF pressure, and associated with severe headache

In a study of 15 normal pressure hydrocephalus patients by Chen *et al* [Chen, 1994] no complications due to the drainage procedure were noted.

Bateman RJ *et al.* reported in a population of 20 healthy volunteers undergoing frequent CSF samplings for assessment of the effect of an amyloid beta modulating agent on CSF amyloid beta levels:

- Four postlumbar puncture headaches
- one episode each of dizziness and numbness requiring follow-up magnetic resonance imaging
- increased blood pressure, back and leg pain, and nausea and vomiting in an unspecified number of cases

All adverse events resolved and were considered by Bateman RJ *et al.* as likely being related to lumbar CSF sampling. Nevertheless, as drug administration was part of the study relationship with the study medication cannot be excluded.

## 7.8. Pharmacogenetics

Information regarding pharmacogenetic (PGx) research is included in [Appendix 1](#). The IEC and, where required, the applicable regulatory agency must approve the PGx assessments before these can be conducted at the site. In some cases, approval of the PGx assessments can occur after approval is obtained for the rest of the study. If so, then the written approval will clearly indicate approval of the PGx assessments is being deferred and in most cases, the study, except for PGx assessments, can be initiated. When PGx assessments will not be approved, then the approval for the rest of the study will clearly indicate this and therefore, PGx assessments will not be conducted.

## 8. LIFESTYLE AND/OR DIETARY RESTRICTIONS

The Investigator (or designated study physician) must be informed as soon as possible about any concomitant medication taken from the time of screening until the end of the clinical phase of the study (follow-up visit).

### 8.1. Contraception Requirements

#### 8.1.1. Contraceptive Methods For Female Subjects Of Childbearing Potential

Female subjects of childbearing potential must not become pregnant and so must be sexually inactive by abstinence or use contraceptive methods with a failure rate of < 1%.

##### Abstinence

Sexual inactivity by abstinence must be consistent with the preferred and usual lifestyle of the subject. Periodic abstinence (e.g. calendar, ovulation, symptothermal, post-ovulation methods) and withdrawal are not acceptable methods of contraception.

##### Contraceptive Methods with a Failure Rates of < 1%

- Oral contraceptive, either combined or progestogen alone
- Injectable progestogen
- Implants of levonorgestrel
- Estrogenic vaginal ring
- Percutaneous contraceptive patches
- Intrauterine device (IUD) or intrauterine system (IUS) that meets the <1% failure rate as stated in the product label
- Male partner sterilization (vasectomy with documentation of azoospermia) prior to the female subject's entry into the study, and this male is the sole partner for that subject. For this definition, “documented” refers to the outcome of the investigator's/designee’s medical examination of the subject or review of the subject's medical history for study eligibility, as obtained via a verbal interview with the subject or from the subject’s medical records.
- Double barrier method: condom and occlusive cap (diaphragm or cervical/vault caps) plus spermicidal agent (foam/gel/film/cream/suppository)

**These allowed methods of contraception are only effective when used consistently, correctly and in accordance with the product label. The investigator is responsible for ensuring subjects understand how to properly use these methods of contraception.**

### **8.1.2. Contraceptive Methods For Male Subjects With Partners Of Childbearing Potential**

To prevent pregnancy in a female partner or to the investigational product from a male subject's semen, male subjects must use one of the following contraceptive methods:

- Abstinence, defined as sexual inactivity consistent with the preferred and usual lifestyle of the subject. Periodic abstinence (e.g. calendar, ovulation, symptothermal, post-ovulation methods) and withdrawal are not acceptable methods of contraception.
- Double barrier method: condom and occlusive cap (diaphragm or cervical/vault caps) plus spermicidal agent (foam/gel/film/cream/suppository)

### **8.2. Meals and Dietary Restrictions**

- Subjects will be required to fast from 2 hours prior to study drug administration until 2 hours post dosing, with the exception of water, which will be allowed freely except for 30 minutes either side of dosing.
- Subjects will be required to eat the standard meals provided by the clinic, no other food is allowed whilst the subject stays at the study clinic.

### **8.3. Alcohol and Tobacco**

- Subjects will abstain from alcohol for 24 hours prior to the start of dosing until collection of the final pharmacokinetic and or pharmacodynamic sample at each visit.
- Subjects who use tobacco products will be instructed that use of nicotine-containing products (including nicotine patches) will not be permitted while they are in the Clinical Unit.

### **8.4. Activity**

Subjects will abstain from strenuous exercise for 48 hours prior to each blood collection for clinical laboratory tests. Subjects may participate in light recreational activities during studies (e.g., watch television, read).

### **8.5. Other restrictions**

- Subjects must refrain from all recreational drugs throughout the study (screening to follow-up). Drugs of abuse tests may be performed randomly throughout the study at the investigators discretion. A positive result at any point will lead to exclusion from the study.

## **9. CONCOMITANT MEDICATIONS AND NON-DRUG THERAPIES**

### **9.1. Permitted Medications**

Paracetamol at doses of  $\leq 2$  grams/day is permitted. Other concomitant medication may be considered on a case by case basis by the GSK Medical Monitor.

All concomitant medications taken during the study will be recorded in the CRF. The minimum requirement is that drug name and the dates of administration are to be recorded.

For details of concomitant medications permitted during the study, please refer to the Exclusion Criteria, Section [5.2.2](#).

### **9.2. Prohibited Medications**

Subjects must abstain from taking prescription or non-prescription drugs (including vitamins and dietary or herbal supplements), within 7 days (or 14 days if the drug is a potential enzyme inducer) or 5 half-lives (whichever is longer) prior to the first dose of study medication until completion of the follow-up visit, unless in the opinion of the Investigator and sponsor the medication will not interfere with the study.

All concomitant medications taken during the study will be recorded in the CRF. The minimum requirement is that drug name and the dates of administration are to be recorded.

For details of concomitant medications not permitted during the study, please refer to the Exclusion Criteria, Section [5.2.2](#).

## **10. COMPLETION OR EARLY WITHDRAWAL OF SUBJECTS**

### **10.1. Subject Completion**

A completed subject is one who has completed all phases of the study including the follow-up visit. Subjects who are screened, but choose not to continue participation in the study will be considered “screen failures”.

The end of the study is defined as the last subject’s last visit.

### **10.2. Subject Withdrawal Criteria**

Refer to Section [4.5](#) for dose adjustment/stopping criteria based on safety criteria.

A subject may withdraw from investigational product at any time at his/her own request, or may be withdrawn at any time at the discretion of the investigator for safety, behavioral or administrative reasons.

### **10.3. Subject Withdrawal Procedures**

#### **10.3.1. Subject Withdrawal from Study**

If a subject does not complete all study procedures then the subject will be considered to have prematurely discontinued from the study. If a subject is prematurely discontinued from participation in the study for any reason, the investigator must make every effort to perform the following evaluations: physical examination, neurological examination, vital signs (supine blood pressure, heart rate and body temperature), ECG, clinical chemistry, haematology, urinalysis, cognitive function tests and AE assessment.

Before discontinuing a subject from study, the Investigator must contact the GSK Medical Monitor. In the event that the investigator is unable to reach the GSK Medical Monitor, the Investigator will make a decision at his or her discretion, until the GSK Medical Monitor can be contacted.

#### **10.3.2. Subject Withdrawal from Investigational Product**

This is single dose study and subject withdrawal will not apply from investigational product. However, if a subject has any safety consideration after his/her first dose (e.g. clinically significant deterioration in cognition, abnormal results from safety lab tests or liver function tests) he/she will not be enrolled into the next dose group.

### **10.4. Treatment After the End of the Study**

Subjects will not receive any additional treatment after completion of the study because GSK933776 is not fully developed and not available in the market. Other treatment options for AD are available.

### **10.5. Screen and Baseline Failures**

Data for screen and baseline failures will be collected in source documentation at the site but will not be transmitted to GSK or electronic database e.g. InForm.

## **11. INVESTIGATIONAL PRODUCT(S)**

GSK933776 at 50 mg/ml will be supplied by GSK in 2 ml or 3ml type 1 glass vials with stopper and aluminium over seals with a 1 mL fill. The physical, chemical and pharmaceutical properties and characteristics of GSK933776 are provided in the Clinical Investigator's Brochure (CIB)

Investigational product dosage and administration details are also listed in Section [4.4](#).

### **11.1. Blinding**

This will be an open-label study.

## **11.2. Packaging and Labeling**

The contents of the label will be in accordance with all applicable regulatory requirements.

## **11.3. Preparation/Handling/Storage/Accountability**

A description of the methods and materials required for preparation of GSK933776 i.v. solution is provided in the SPM.

Investigational product must be dispensed or administered according to procedures described herein. Only subjects enrolled in the study may receive investigational product. Only authorized site staff may supply or administer investigational product. All investigational products must be stored in a secure area with access limited to the investigator and authorized site staff. Investigational product is to be stored at 2-8°C and protected from light. Maintenance of a temperature log is required.

The investigator is responsible for investigational product accountability, reconciliation, and record maintenance. The investigator or designated site staff must maintain investigational product accountability records throughout the course of the study. The responsible person(s) will document the amount of investigational product received from GSK and the amount supplied and administered. The required accountability unit for this study will be individual vials. Discrepancies are to be reconciled or resolved. Procedures for final disposition of unused investigational product are listed in the SPM.

Investigational product is not expected to pose significant occupational safety risk to site staff under normal conditions of use and administration. However, precaution should be taken to avoid direct contact with the investigational product. A Material Safety Data Sheet (MSDS)/equivalent document describing occupational hazards and recommended handling precautions either will be provided to the investigator, where this is required by local laws, or is available upon request from GSK.

Precaution will be taken to avoid direct contact with the investigational product. A Material Safety Data Sheet (MSDS) describing occupational hazards and recommended handling precautions will be provided to the investigator.

## **11.4. Assessment of Compliance**

The individual dose for a subject is prepared from a bulk supply, thus, the correct preparation of the dose will be confirmed and documented by a second member of the study site staff.

Subjects are to be dosed at the study site, where they will receive investigational products directly from the investigator or designee, under medical supervision. The date and time of dosing will be recorded in the source documents. The dose of investigational product(s) and study participant identification will be confirmed at the time of dosing by a member of the study site staff other than the person administering the investigational product.

## 11.5. Treatment of Investigational Product Overdose

For this study, any dose of GSK933776 > 6mg/kg within a 24 hour time period [ $\pm$  1 hour] will be considered an overdose.

GSK does not recommend specific treatment for an overdose. The investigator will use clinical judgment to treat any overdose.

## 12. ADVERSE EVENTS (AE) AND SERIOUS ADVERSE EVENTS (SAE)

The investigator or site staff is responsible for detecting, documenting and reporting events that meet the definition of an AE or SAE.

AEs will be collected from the insertion of CSF catheter and until the follow-up contact. Medical occurrences that begin prior to the start of investigational product but after obtaining informed consent may be recorded on the Medical History/Current Medical Conditions CRF.

SAEs will be collected over the same time period as stated above for AEs. However, any SAEs assessed as related to study participation (e.g. investigational product, protocol-mandated procedures, invasive tests, or change in existing therapy) or related to a GSK concomitant medication will be recorded from the time a subject consents to participate in the study up to and including any follow-up contact. All SAEs will be recorded and reported to GSK within 24 hours, as indicated in Section 12.7.

Investigators are not obligated to actively seek AEs or SAEs in former study participants. However, if the investigator learns of any SAE, including a death, at any time after a subject has been discharged from the study, and he/she considers the event reasonably related to the investigational product or study participation, the investigator would promptly notify GSK.

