|                                                                        |                                                          |                                                                                                                         | 1 h                             | 2 h | 3 h | 4 h | 5 h | 6 h | 7 h | 8 h |      | 9 h                              | 10 h | 11 h | 12 h | 13 h | 14 h | 15 h | 16 h | 17 h | 18 h | 19 h | 20 h | 21 h                    | 22 h | 7 days |
| Pharmacodynamics CSF – total tau and phosphorylated tau 181            |                                                          |                                                                                                                         |                                 |     |     | x   |     |     |     |     | x    |                                  |      |      |      | x    |      |      |      |      |      |      |      | x                       |      |        |
| Pharmacodynamics CSF– amyloid beta fragments and isoforms by IP- MALDI |                                                          | ----Selected samples will be analysed based on the results of free and total amyloid beta 1-42 measurements in CSF----- |                                 |     |     |     |     |     |     |     |      |                                  |      |      |      |      |      |      |      |      |      |      |      |                         |      |        |
| CSF sampling for PK                                                    |                                                          |                                                                                                                         |                                 |     |     |     |     |     |     |     | x    |                                  |      | x    | x    | x    | x    |      | x    | x    | x    | x    | x    | x                       |      |        |

1. If a subject will be enrolled into the next dose group within 6 months, screening for MRI, HIV, Hep B, Hep C and Syphilis test are not requested.
2. Vital signs will include systolic and diastolic blood pressure, pulse rate and oral (or tympanic) body temperature.
3. Exact dose time will be immediately after last baseline (7 - 11 hour) sample.

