## **12.5. Evaluating AEs and SAEs**

### **12.5.1. Assessment of Intensity**

The investigator will make an assessment of intensity for each AE and SAE reported during the study and will assign it to one of the following categories:

Mild: An event that is easily tolerated by the subject, causing minimal discomfort and not interfering with everyday activities.

Moderate: An event that is sufficiently discomfoting to interfere with normal everyday activities.

Severe: An event that prevents normal everyday activities.

An AE that is assessed as severe will not be confused with an SAE. Severity is a category utilized for rating the intensity of an event; and both AEs and SAEs can be assessed as severe. An event is defined as 'serious' when it meets at least one of the pre-defined outcomes as described in the definition of an SAE.

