## **12.7. Prompt Reporting of SAEs to GSK**

Once the investigator determines that an event meets the protocol definition of an SAE, the SAE will be reported to GSK **within 24 hours**. Any follow-up information on a previously reported SAE will also be reported to GSK within 24 hours.

If the investigator does not have all information regarding an SAE, he/she will not wait to receive additional information before notifying GSK of the event and completing the appropriate data collection tool. The investigator will always provide an assessment of causality at the time of the initial report as described in Section [12.5.2](#), Assessment of Causality.

The primary mechanism for reporting SAEs to GSK will be the electronic data collection tool (e.g., InForm system). If the electronic system is unavailable for greater than 24 hours, the site will use the paper SAE data collection tool and fax it to the GSK Medical Monitor or protocol contact. Then the site will enter the serious adverse event data into the electronic system as soon as it becomes available.

After the study is completed at a given site, the electronic data collection tool (e.g., InForm system) will be taken off-line to prevent the entry of new data or changes to existing data. If a site receives a report of a new SAE from a study participant or receives updated data on a previously reported SAE after the electronic data collection tool has been taken off-line, the site can report this information on a paper SAE form or to their GSK protocol contact by telephone.

GSK contacts for SAE receipt can be found at the beginning of this protocol on the Sponsor/Medical Monitor Contact Information page.

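### AE collection opens only at catheter insertion, so non-serious harm from the screening lumbar puncture needs no AE record, and Section 10.5 conflicts with the SAE rule for screen failures

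*Protocol*

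**What the plan says.** Protocol Section 12 sets the window: "AEs will be collected from the insertion of CSF catheter and until the follow-up contact". For occurrences after consent but before the investigational product, it says only that they "may be recorded on the Medical History/Current Medical Conditions CRF". The general SAE window is the same as the AE window. There is one extension: "any SAEs assessed as related to study participation (e.g. investigational product, protocol-mandated procedures, invasive tests, or change in existing therapy") or related to a sponsor concomitant medication are recorded from consent onward. All SAEs must reach the sponsor within 24 hours. Section 12.7 gives the route: "The primary mechanism for reporting SAEs to GSK will be the electronic data collection tool (e.g., InForm system").

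Section 10.5 deals with screen and baseline failures. Their data are kept in source documents at the site and "will not be transmitted to GSK or electronic database", InForm being the example given. It makes no exception for SAEs.

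The screening lumbar puncture is a study procedure. Inclusion criterion 2 (Section 5.2.1) needs CSF amyloid beta 1-42 and tau values, and Section 7.2.6 confirms that these results decide entry. The Time and Events Table (Section 4.6) places it in screening, up to 30 days before Day 1. On its main risk, Section 7.7 says: "Published data indicates the incidence of headache in subjects following diagnostic lumbar puncture ranges from 3.3 to 59.2" per cent.

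**The concern.** The protocol mandates two spinal procedures, the screening puncture and the later catheter with continuous drainage. Only the second falls inside the AE window. For the first, a non-serious complication can at most become an optional medical-history entry. That places it outside Section 12.5.1, under which "The investigator will make an assessment of intensity for each AE and SAE reported during the study", and outside the causality assessment in Section 12.5.2. Section 1.3.3 rests part of the benefit-risk case on lumbar puncture events being infrequent and mostly mild. The study would not reliably collect the non-serious data that could check this for the screening puncture.

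The second problem is a conflict between two instructions. Suppose a candidate has a serious complication of the screening puncture and then fails screening. Section 12 tells the site to send the SAE to the sponsor within 24 hours, and Section 10.5, read literally, tells it to send nothing. A safety-reporting rule with a 24-hour limit should not leave the site to work out which instruction prevails.

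**Working it through.** **The AE window.** The order of events for an enrolled subject is:

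1. Consent, then the screening lumbar puncture, up to 30 days before Day 1 (Section 4.6).
2. Admission and catheter insertion. AE collection starts here (Section 12).
3. About 9 hours of baseline sampling, then dosing (Section 4.2).

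Step 1 lies wholly before AE collection. The Adverse Event Review row of the Time and Events Table has no entry at screening. Section 1.3.4 ties AE monitoring to the time the catheter is in place and to drug exposure. The three places agree, so this is how the plan is set.

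For that interval:

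| Type of event | Required record |
|---|---|
| SAE related to a mandated procedure | Yes, from consent (Section 12) |
| Non-serious event from the screening puncture | None; medical-history entry optional |
| Later worsening of an earlier headache | Yes, as an AE once the window is open (Section 12.1) |
| Headache from catheter or drainage | Yes, inside the window |

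The gap is the second row.

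**Scale.** The protocol gives no figure of its own to reproduce. The calculation below is an illustration.

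- Enrolled subjects: n = 20 to 35 (Section 5.1).
- Headache probability per diagnostic puncture: p = 0.033 to 0.592 (Section 7.7).
- One screening puncture per subject, subjects independent.
- Expected count = n × p. Chance of at least one = 1 − (1 − p)^n.

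| n | p | Expected headaches | Chance of at least one |
|---|---|---|---|
| 20 | 0.033 | 20 × 0.033 = 0.66 | 1 − 0.967^20 = 0.489 |
| 35 | 0.033 | 35 × 0.033 = 1.16 | 1 − 0.967^35 = 0.691 |
| 20 | 0.592 | 20 × 0.592 = 11.84 | about 1.00 |
| 35 | 0.592 | 35 × 0.592 = 20.72 | about 1.00 |

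Two groups are left out, and both would raise the counts. Candidates who fail screening after the puncture are not included, as their number is not given. Nor are repeat punctures in subjects who re-enter a later dose group within 6 months: footnote 1 of the Time and Events Table says that "screening for MRI, HIV, Hep B, Hep C and Syphilis test are not requested", and the CSF sample is not on that list.

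**The reporting conflict.** Take a candidate with a serious puncture complication who then fails the CSF criterion or declines to continue. Section 10.1 classes the latter as a screen failure.

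- Section 12: a related SAE, recorded from consent and sent to the sponsor within 24 hours.
- Section 12.7: sent primarily through InForm.
- Section 10.5: nothing sent to the sponsor or to InForm.

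The paper and telephone routes in Section 12.7 do not remove the conflict. They cover InForm being unavailable or taken off-line, whereas Section 10.5 bars transmission to the sponsor by any route. Failing screening after the puncture is an ordinary outcome here, because the puncture result is itself an entry criterion. A serious complication in such a person would be rare, and no rate for it is given.

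**The case against.** On the AE window, the safety objective concerns GSK933776 and not lumbar puncture, and Section 12.1 defines an AE by its timing relative to a medicinal product. A headache weeks before dosing arguably falls outside that definition. The protocol calls the literature on drainage catheters limited, while it cites published incidence and prevention reports for diagnostic puncture, so opening the window at the catheter could be a reasoned choice. Related SAEs are covered from consent, Appendix 6 gives the investigator responsibility for managing puncture-related events, and medical history and concomitant-medication records exist.

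The argument from the definition does not stand. The protocol already collects AEs from catheter insertion, hours before dosing, and procedure-related SAEs from consent, so it accepts procedural harm before dosing as reportable. The remaining points limit the size of the gap but do not close it, since none creates a required AE entry.

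On Section 10.5, the ordinary reading would let the specific SAE duty override a general data-handling sentence. Section 12 also asks for prompt notification of a related SAE learned of after discharge. That reading is plausible and many sites would adopt it, but the protocol does not state it, and the post-discharge paragraph repeats the duty without lifting the bar.

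On scale, the headache range is published and not site-specific. Section 7.7 says needle size and shape matter and that prevention guidance will be considered, so the upper figures are an extreme. The 49% to 69% is the chance that a headache occurs before the window, not that it goes unrecorded everywhere.

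**Conclusion.** Both parts hold, and both are minor. The AE data will not reliably contain non-serious harm from the screening puncture. At the lowest cited rate that means about one headache across the study; at the highest, 12 to 21. These figures assume one puncture per enrolled subject, independence between subjects and the published range; the rate at the study sites is not given. Section 10.5 is wrong as written, because it contains no exception for SAEs that Section 12 requires to be sent. The primary CSF endpoint and the drug-related stopping rules are unaffected.

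**What to change.** Add one sentence to Section 12: *AEs related to protocol-mandated procedures, serious or not, will be collected from the screening lumbar puncture and reported separately as pre-dose procedural events.* Separate reporting keeps them out of the post-dose AE tables.

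Add one clause to Section 10.5: *except procedure-related AEs, and SAEs related to study participation, which are reported as in Sections 12 and 12.7.*

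The Adverse Event Review row of the Time and Events Table would need a matching screening entry. The cost is two sentences in the next amendment, a few CRF entries, and a minimal record for any screen failure who has such an event. The downside is slightly more data entry and a less favourable procedural AE rate.
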